### MEG data acquisition

#### Language tasks

Prior to data recording, participants will be instructed to close their eyes, relax while remaining awake, focus their attention, and minimize head movement and facial muscle activity. A 5 min resting-state MEG recording will be collected. Each participant will then complete two cognitive tasks.

*Picture naming task*: Participants will view black-and-white line drawings from the Snodgrass and Vanderwart (S&V) database presented sequentially on a projection screen. Prior to the formal experiment, a pilot test was conducted among native Chinese speakers to assess picture-naming agreement, and only culturally familiar and unambiguous drawings with high naming agreement were selected for the experiment. They will be asked to name each picture verbally as quickly as possible following its appearance. The task consists of 100 trials with a randomized stimulus order, divided into two blocks of 50 trials with a short rest between blocks to reduce participant fatigue. Each trial begins with a central fixation cross presented for 500 ms, followed by the target picture presented for 1,500 ms. Participants are required to name the picture during or immediately after its presentation. The inter-trial interval is 3,000 ms. MEG signals will be recorded simultaneously throughout the task.

*Language repetition task*: Participants will listen to spoken words through earphones, selected from the Western Aphasia Battery (WAB) and the Chinese Rehabilitation Research Center Aphasia Examination (CRRCAE) repetition items. Prior to the formal experiment, a pilot test was conducted among native Chinese speakers to assess word familiarity, and only highly familiar and unambiguous items were selected for the experiment. All stimuli are spoken Mandarin Chinese with item length fixed at two characters and an acoustic duration of approximately 660 ms. They will be asked to repeat the auditory stimuli as quickly and accurately as possible after presentation. Each trial begins with a 500-ms fixation cue, followed by the target auditory stimulus, and then a 1,500–2,000 ms response window. The inter-trial interval is 1,000 ms. The task consists of 100 trials with simultaneous MEG recording, divided into two blocks of 50 trials with a short rest between blocks to reduce participant fatigue.

#### Resting-state recording

Each resting-state recording will last 5 min. To evaluate the effects of acupuncture intervention, each participant will complete one resting-state recording before and one after the acupuncture intervention.

#### Acupuncture-state recording

During the acupuncture task, participants will lie supine on the scanning bed, keeping their head stable and remaining as relaxed as possible. Before data collection, the investigator will explain the entire procedure and inform participants about the acupoint locations and needling sequence. All acupuncture procedures will be performed by a qualified acupuncturist according to the pre-determined protocol.

#### MEG acquisition parameters

MEG data will be acquired using the PyraMag Epoch 64 system (Quanmag Healthcare Co. Ltd., Beijing, China), equipped with 64 optically pumped magnetometer (OPM) sensors presented in Figure 4. The sampling rate will be set at 1000 Hz. The sensors are uniformly distributed across a helmet to achieve whole-brain coverage. Participants will lie comfortably on the scanning bed in a quiet environment. Prior to the formal acquisition, a 3D facial point cloud will be obtained for each participant using an optical scanning system (FreeScan Combo, Shining 3D Technology Co., Ltd., Hangzhou, China) for subsequent co-registration of OPM-MEG data with individual T1-weighted structural MRI images. After acquiring the facial point cloud, participants will be moved into the magnetically shielded cylinder to begin MEG recording.

**Figure 4 fig4:**
[figure not shown]
Spatial distribution of sensors within the MEG helmet.

#### MRI acquisition parameters

Structural MRI data will be acquired on a Siemens Skyra 3.0 T scanner using a 32-channel phased-array head coil. 3D T1-weighted images will be obtained using a magnetization-prepared rapid gradient echo (MPRAGE) sequence with the following parameters: repetition time (TR)/echo time (TE) = 1,900/2.2 ms; flip angle = 9°; slice thickness = 1 mm; matrix size = 256 × 256; field of view (FOV) = 256 × 256 mm^2^. During scanning, participants will be asked to close their eyes, relax, and remain awake. Earplugs will be provided to reduce noise, and foam padding will be used to minimize head motion.

### Outcome measures

#### Primary outcome

The primary outcome is the change in MEG signals before and after acupuncture intervention. MEG data will be collected during the resting state, acupuncture state, and language task state to evaluate the central effects of acupuncture. Specific MEG metrics include power spectral density (PSD) across different frequency bands (delta: 1–4 Hz, theta: 4–8 Hz, alpha: 8–13 Hz, beta: 13–30 Hz, gamma: 30–80 Hz), source-space neural activity, and whole-brain functional connectivity.

#### Secondary outcome

The secondary outcome is the C-MASS, assessed in both the VA and SA groups, which will be used to quantify participants’ subjective acupuncture sensations (*deqi*). The C-MASS scores will be used for subsequent correlation analysis with MEG metrics to explore the relationship between acupuncture sensation and central neural responses.

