XiaJiquan (Lower HT1, bilateral)	On the anterior upper arm, 1–2 cun inferior to Jiquan (HT1), along the line connecting Jiquan (HT1) and Shaohai (HE3)	Perpendicular insertion 1.0–1.5 cun; lifting-thrusting reducing method until 3 involuntary limb twitches are elicited	No retention
Chize (LU5, bilateral)	On the cubital crease, radial to the biceps brachii tendon	Perpendicular insertion 0.5–0.8 cun with elbow flexed at 120°; lifting-thrusting reducing method until 3 involuntary forearm twitches	No retention
Weizhong (BL40, bilateral)	At the midpoint of the popliteal crease, between the biceps femoris and semitendinosus tendons	Perpendicular or oblique insertion 1.0–1.5 cun with leg elevated and extended; lifting-thrusting reducing method until 3 involuntary limb twitches	No retention
Lianquan (CV23)	On the anterior midline, in the depression above the hyoid bone, superior to the thyroid cartilage	Perpendicular insertion 2.0 cun; lifting-thrusting and twirling-rotating to achieve *deqi*	30 min
PangLianquan (Beside CV23, bilateral)	0.5 cun lateral to Lianquan, in the depression above the notch of the thyroid cartilage	Perpendicular insertion 1.0–1.5 cun; lifting-thrusting and twirling-rotating to achieve *deqi*	30 min

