#### SA group

Considering the practical constraints of the Xingnao Kaiqiao multi-acupoint protocol, in which spring-type placebo needles or skin-adhesive sham devices are not feasible and may compromise blinding, the SA control was designed based on published international acupuncture clinical trial protocols (10). The SA group will receive superficial needling at non-acupoints located 1 cun (approximately 20 mm, using the participant’s proportional measurement) lateral to each corresponding verum acupoint. The same type of needle (0.30 × 40 mm; Hwato Brand) will be used, and the procedure will be performed by the same qualified acupuncturist.

At each sham acupoint, the needle will be inserted superficially to a depth of 0.2–0.3 cun (approximately 4–6 mm), sufficient only to suspend the needle in the skin. No manual manipulation will be applied, and participants should not experience *deqi* sensation. Bilateral simultaneous needling and needle retention durations will be identical to the VA group. The single-acupoint sequence will be performed first, followed by the multi-acupoint sequence, consistent with the VA protocol.

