### Statistical analysis

For the resting-state PSD values, source-space neural activity, and whole-brain functional connectivity indices, both within-group and between-group comparisons will be performed. For within-group comparisons of pre- and post-acupuncture paired data, paired *t*-tests will be used. For between-group comparisons of the VA and SA groups, independent-sample *t*-tests will be employed. In whole-brain source-space statistical analyses, permutation-based cluster correction (≥5,000 permutations) will be applied to control for multiple comparisons and to identify brain regions with statistically significant differences.

For task-state data, time-window-based statistical methods will be used to compare brain activation intensity at different post-stimulus stages (time windows from 0 to 1,000 ms, in 100-ms steps). Linear mixed models will be applied to analyze condition effects and their interactions.

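### The planned C-MASS–MEG correlation has no arm term, although the arms are built to differ in needling sensation; run across both arms unadjusted, it would be confounded by arm

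*Protocol article*

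**What the plan says.** Under Secondary outcome, "The secondary outcome is the C-MASS, assessed in both the VA and SA groups". The same section then says that "The C-MASS scores will be used for subsequent correlation analysis with MEG metrics", and gives the purpose as "to explore the relationship between acupuncture sensation and central neural responses". It names no coefficient, analysis set or covariate.

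The two arms are described under Interventions:

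- **Sham (SA group):** "the needle will be inserted superficially to a depth of 0.2–0.3 cun". The section continues: "No manual manipulation will be applied, and participants should not experience" *deqi* sensation. The sites are also moved 1 cun away from the verum points.
- **Verum (VA group, Table 1):** the technique at CV23 and Beside CV23 is "lifting-thrusting and twirling-rotating to achieve" *deqi*. GV26 is stimulated until the eyes water, and Lower HT1, LU5 and BL40 until three twitches are seen.

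The Statistical analysis section tests MEG metrics by arm ("For between-group comparisons of the VA and SA groups, independent-sample" *t*-tests) and uses linear mixed models for the task data. It does not mention the C-MASS correlation.

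Two Discussion sections return to it. The one on *deqi* and MEG says the study will look at whether *deqi* goes with particular oscillations or regional activity. The one on implications says that an association, if found, may help tune needling parameters in later clinical studies.

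**The concern.** The design pushes C-MASS up in one arm and down in the other. Assignment also changes needle depth, site, manipulation, tearing and twitching, and each of these could alter MEG without acting through *deqi*. Arm is therefore a common cause of the predictor and, if the trial's main hypothesis is right, of the outcome as well.

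A single correlation over both arms mixes two things: the association among people who had the same type of needling, and the difference between the two types. Only the first speaks to whether sensation as such relates to brain response. The second repeats the verum–sham comparison that the trial already makes.

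At stake is the interpretation of the only analysis that links *deqi* to MEG. A positive pooled result could be reported as a neural correlate of *deqi*, and carried into later work, when it shows only that verum differs from sham.

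**Working it through.** **Inputs from the protocol.** Sample size calculation gives 40 enrolled at 1:1 and 20% dropout. Check: 40 × (1 − 0.20) = 32, or 16 per arm, which agrees with the stated figure. No effect size, SD, alpha or power is given there, and no figure of any kind for the correlation, so nothing further can be reproduced.

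**Assumed inputs.** D is the verum–sham gap in C-MASS and d the gap in a MEG metric, both in within-arm SD units. The documents give neither, so a range is shown. The test is two-sided at 5%, and the true within-arm correlation is set to zero.

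**Formula.** With equal arms and no within-arm association, the between-arm covariance is D·d/4 and the total variances are 1 + D²/4 and 1 + d²/4. Hence

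pooled r = (D·d/4) / √[(1 + D²/4)(1 + d²/4)]

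- D = 1, d = 0.5: 0.125 / √(1.25 × 1.0625) = 0.11
- D = 2, d = 0.8: 0.40 / √(2 × 1.16) = 0.26
- D = 3, d = 0.8: 0.60 / √(3.25 × 1.16) = 0.31

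**Rejection rates.** These come from 20,000 simulated trials per cell, with normal data, comparing pooled Pearson with the partial correlation given arm.

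| D (C-MASS) | d (MEG) | pooled r | pooled, 16 / 20 per arm | arm-adjusted, 16 / 20 per arm |
|---|---|---|---|---|
| 0.5 | 0.5 | 0.06 | 6.1% / 6.6% | 4.8% / 5.0% |
| 1 | 0.5 | 0.11 | 9.1% / 10.2% | 5.0% / 5.3% |
| 1 | 0.8 | 0.17 | 15.2% / 17.8% | 5.1% / 5.1% |
| 2 | 0.5 | 0.17 | 15.3% / 18.7% | 4.8% / 4.8% |
| 2 | 0.8 | 0.26 | 32.0% / 39.3% | 4.9% / 4.8% |
| 3 | 0.8 | 0.31 | 43.3% / 52.2% | 5.1% / 5.0% |

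If either gap is zero, the pooled rate stays at about 5% (4.7–5.3%). Over all cells simulated, the adjusted rate lay between 4.7% and 5.4%.

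**Correlation detectable with 80% power.** The Fisher approximation is r = tanh[(1.96 + 0.8416)/√(N − 3)], with N − 4 in place of N − 3 after adjusting for arm.

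- Both arms, N = 32: 0.478 unadjusted, 0.485 adjusted.
- Both arms, N = 40: 0.431 unadjusted, 0.436 adjusted.
- Verum only: 0.651 with 16, 0.591 with 20.

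**The case against.** The strongest reply is that the protocol never says the arms are pooled. That C-MASS is "assessed in both the VA and SA groups" is a statement about data collection, and it also lets the trial check that sham needling does avoid *deqi*. A verum-only, per-arm or arm-adjusted correlation would fit the wording too. The article is condensed, an analysis plan may exist, and the details of an exploratory correlation often sit there.

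Much of this stands. A reader might infer that the plan has committed itself to a pooled analysis; the text does not support that. A reader might also infer that any arm effect on MEG will show up as a *deqi* association. That is too strong, because both gaps must be non-zero, and with a sensation gap of 0.5 SD and MEG gaps of 0.5–1.0 SD the rate is only 6–11%. Nor does the protocol claim it will conclude that *deqi* drives MEG: its language is exploratory and conditional.

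A further fair point is mediation. If *deqi* is a route by which verum needling changes MEG, part of a pooled correlation is real, and adjusting for arm leaves that part out. But the pooled coefficient cannot separate it from the effects of depth, site and manipulation.

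The objection does not remove the point. All the scores are assigned to a correlation in unrestricted terms, the plainest way of carrying that out is the confounded one, and nothing elsewhere in the document guards against it. Calling the analysis exploratory does not correct the bias.

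**Conclusion.** The point holds conditionally. The protocol leaves open how arm is handled in the C-MASS–MEG correlation, and the analysis its wording most readily suggests would be confounded by arm.

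If it is run that way, the expected spurious r is about 0.11–0.31 and the false-positive rate about 9–52%, for assumed gaps of 1–3 SD on C-MASS and 0.5–0.8 SD on MEG with 16 to 20 per arm. These figures rest entirely on the assumed gaps, on normal data and on a zero within-arm association. That the arms will differ in C-MASS is an inference from how they are built, not a reported result; *deqi* is the stated endpoint of manipulation only at CV23 and Beside CV23.

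This affects an exploratory secondary analysis. It does not touch the randomised comparison of verum with sham, and it is best treated as a cheap improvement.

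**What to change.** Add one sentence to Statistical analysis: the association between C-MASS and each MEG metric will be estimated with adjustment for arm, either as a partial correlation or as a regression of the MEG metric on C-MASS with arm as a covariate. Report a C-MASS-by-arm term and the verum-only estimate as supporting results, and state that an unadjusted pooled correlation will not be interpreted as a *deqi* effect.

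The verum-only estimate should not be the main result, since 80% power there needs a correlation of about 0.59–0.65.

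The cost is small. At N = 32 the detectable correlation moves from about 0.48 to 0.49. The interval for a regression slope widens as well, because the between-arm spread in C-MASS no longer counts: at equal residual variance the factor is √(1 + D²/4), for example √2 = 1.41 if D = 2. The precision given up is the part that came from the confounded contrast. Any *deqi* effect carried between the arms is also left out, and the report should say so.

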### Data analysis

#### MEG data preprocessing

MEG data will be preprocessed using the Brainstorm toolbox (based on MATLAB). First, zero-phase finite impulse response (FIR) notch filters will be applied at 50–250 Hz (in steps of 50 Hz) to remove power-line noise and its harmonics. A band-pass filter of 1–80 Hz will then be applied to retain frequencies of interest. The raw waveforms and power spectral density (PSD) plots of the preprocessed data will be visually inspected, and channels with poor data quality will be rejected. Bad channels will be interpolated using the mean signal from neighboring sensors within a 5-cm radius. Independent component analysis (ICA) will be used to remove physiological artifacts such as cardiac signals, and segments contaminated by muscle artifacts will be excluded from further analysis. Resting-state data will be segmented into 2-s epochs, and task-state data will be segmented into epochs from −500 ms to 1,500 ms relative to stimulus onset (time 0). Epochs containing artifacts will be manually rejected.

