#### Source reconstruction

Individual anatomical MRI data will be processed using FreeSurfer for cortical surface reconstruction and brain tissue segmentation. Co-registration between MEG data and individual MRI will be performed using the facial point cloud. A forward model will be constructed using a boundary element model (BEM) based on each participant’s anatomical MRI. Source reconstruction will be performed using the dynamic Statistical Parametric Mapping method to obtain distributed source activity across the cortical surface.

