#### Resting-state analysis

For resting-state data, PSD values will be calculated for the delta (1–4 Hz), theta (4–8 Hz), alpha (8–13 Hz), beta (13–30 Hz), and gamma (30–80 Hz) bands. These values will be used to assess changes in spontaneous neural oscillatory activity after acupuncture. Source-level PSD will be analyzed to show the spatial distribution of spontaneous neural oscillatory activity. Functional connectivity in source space will be estimated with the phase locking index (PLI) to characterize large-scale brain network organization.

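### Bad MEG channels are filled with the plain mean of sensors within 5 cm and apparently passed to dSPM as if measured; for source analysis, leaving them out is modestly better

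*Protocol article*

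**What the plan says.** The Protocol article, MEG data preprocessing, has waveforms and spectra inspected by eye, after which "channels with poor data quality will be rejected". The replacement rule is explicit: "Bad channels will be interpolated using the mean signal from neighboring sensors within a 5-cm radius". ICA and epoching are described after this step.

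The system is "equipped with 64 optically pumped magnetometer (OPM) sensors" (MEG acquisition parameters), and "The sensors are uniformly distributed across a helmet to achieve whole-brain coverage". The distance between sensors is not given.

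The next section, Source reconstruction, states: "Source reconstruction will be performed using the dynamic Statistical Parametric Mapping method to obtain distributed source activity across the cortical surface". It does not say which channels enter the inverse.

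The primary outcome lists band power, "source-space neural activity, and whole-brain functional connectivity". The Resting-state analysis section adds: "Source-level PSD will be analyzed to show the spatial distribution of spontaneous neural oscillatory activity". It also puts connectivity in source space. Band power is listed there separately from source-level power, without saying whether it is computed at the sensors or in source space.

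**The concern.** The magnetic field of a cortical source has a positive and a negative peak a few centimetres apart. If neighbouring sensors are about 3 cm apart, an unweighted mean over a 5-cm radius flattens a peak or mixes values of opposite sign. The filled value is a linear combination of other channels, so it brings no new information and leaves the data rank-deficient before ICA. If it is then handed to dSPM as a measurement, the inverse must explain a field value that the forward model does not predict at that sensor. dSPM does not need a complete array, so the step buys nothing for source analysis.

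At stake are source activity, source-level power and source connectivity, all of which come from this inverse. The primary outcome is a change from before to after needling. No stated rule keeps the bad-channel set the same across the recordings of a participant, so a channel that is good in one recording and filled in the other produces some apparent change with no change in the brain.

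**Working it through.** The plan gives no interpolation error, no bad-channel count and no sensor spacing, so there is no figure of its own to reproduce. The numbers below rest on assumed geometry.

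**Inputs from the plan.** 64 sensors, uniform layout, plain mean, 5-cm radius, dSPM.

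**Assumptions.** Spherical head; radial sensors on a cap of radius R = 9.7, 10.0 or 10.5 cm, with the cap edge at polar-angle cosine c = −0.2 or −0.35; 1,200 tangential dipoles at 6.0 or 7.5 cm radius; white noise at about one third of RMS signal; 1, 3 or 6 bad channels; sources within 6 cm of a bad sensor.

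**Step 1: spacing and neighbours.** Area per sensor is A = 2πR²(1 − c)/64. Spacing is roughly √A, and the expected number of neighbours within 5 cm is π·5²/A − 1.
- R = 9.7, c = −0.2: A = 709.4/64 = 11.1 cm²; spacing 3.3 cm; neighbours 78.5/11.1 − 1 = 6.1.
- R = 10.5, c = −0.35: A = 935.2/64 = 14.6 cm²; spacing 3.8 cm; neighbours 78.5/14.6 − 1 = 4.4.

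The simulated layouts agree: median nearest-neighbour distance 3.1–3.7 cm, median 5–6 neighbours, minimum 3.

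**Step 2: error of the filled value.** With m neighbours, the filled value is b̂ₖ = (1/m)Σbⱼ. Against the true field its relative RMSE is 0.68–0.82 for nearby sources. Where the lost sensor carries strong signal, the mean returns a median of 0.48–0.54 of the true value.

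**Step 3: rank.** With k filled channels, the 64 channels have rank at most 64 − k; six bad channels give at most 58.

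**Step 4: effect after dSPM.** Ranges over all layouts and 1 to 6 bad channels:

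| Handling | Mean localisation error (mm) | Median amplitude ratio | Map 1 − r² |
|---|---|---|---|
| All sensors good | 9.5–12.1 | 1.00 | 0.17–0.20 |
| Bad channels dropped | 10.0–12.9 | 0.96–0.98 | 0.21–0.24 |
| Plain 5-cm mean | 10.8–13.9 | 0.90–0.96 | 0.23–0.27 |

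Differences within the same layout and bad-channel count:
- Filled minus dropped, localisation: smallest 11.5 − 11.0 = 0.5 mm (R = 10.0, c = −0.2, one bad); largest 13.7 − 12.3 = 1.4 mm (R = 10.5, c = −0.35, six bad).
- Dropped minus filled, amplitude: smallest 0.97 − 0.96 = 0.01; largest 0.96 − 0.90 = 0.06.
- Dropped against all good: 0.3–0.8 mm worse, with 2–4% of amplitude lost.

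A second spherical-head simulation with one bad sensor gave 1.0–1.4 mm and 6–7 points of *mean* amplitude in favour of dropping. In the worst tenth of cases, amplitude fell to 0.65–0.70 of the full-array value when filled and to 0.82–0.86 when dropped.

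**Step 5: change within a participant.** A further noise-free run put one bad sensor within 6 cm of a single dipole. Mean absolute amplitude deviation from the full array was 8–12% with filling and 4–6% with dropping. This is the size of mismatch when a channel is good in one recording and bad in the other. Using the same sensors in both recordings removes it by construction.

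**Step 6: noise or bias.** Let a be the mean attenuation at a source when its nearby sensor is filled, and let p_pre and p_post be the chances that the sensor is bad. The expected spurious change is −a(p_post − p_pre). It is zero if the two chances are equal. The spurious VA–SA difference is the difference of this quantity between arms, and is zero if channel failure does not depend on arm.

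**The case against.** **That filled channels enter dSPM is inferred.** This is so. The article condenses a fuller plan, and which channels feed the inverse is a pipeline detail. But the fill rule, its weighting and its radius are stated, the inverse follows, and nothing shown exempts it. It is the natural reading of a fixed choice.

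**Interpolation can be legitimate.** If band power is compared at sensor level, which the text leaves open, a common sensor set is a fair reason to interpolate for that analysis. This stands and limits the point to source analyses.

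**There is no demonstrated bias.** The rule is the same in both arms, and the Blinding section keeps technicians and analysts unaware of allocation. Random changes in channel status add variance but do not shift a group mean in a set direction. This stands too.

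**Stronger readings to avoid.**
- A reader might infer that dropping a channel is free. It is not: with 64 sensors it costs some coverage and precision, though nothing that the neighbour mean would recover.
- A reader might infer that every source-space primary metric is corrupted. Only recordings with a bad channel are affected, mainly for nearby sources.
- With the bad channel exactly at the field maximum of a superficial dipole, a simulation gives 12.9 mm with filling against 7.3 mm with dropping, and 59% against 79% of amplitude. That is a worst case and not a typical size.
- The 3 to 5 mm precision in the Background is a general statement about MEG. Here the simulated error is already 9.5–12.1 mm with all sensors good, so missing that mark cannot be blamed on interpolation.

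**Conclusion.** The point holds at modest weight. For source analysis, filling bad channels with a plain 5-cm mean is consistently worse than leaving them out, by roughly 0.5–1.4 mm and 1–7 points of amplitude (1–6 on medians, 6–7 on means) for sources near a bad sensor. It acts mainly as avoidable noise and attenuation, in a trial that expects as few as 16 complete participants per group. The documents do not support a claim that the before/after or VA–SA contrast is biased; that would need bad channels to differ systematically by timepoint or arm, and no bad-channel counts are given.

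The direction was the same in every layout tried. The sizes depend on the spherical head, the assumed spacing, the noise level and the number of bad channels, so the net effect on any endpoint is unknown.

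**What to change.** Replace the interpolation sentence with wording such as:

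> For source activity, source-level power and source connectivity, bad channels are excluded from the data and from the corresponding rows of the forward model. Within a participant, recordings that are directly contrasted (for example, each pre/post pair) use the same good channels: a channel bad in either is excluded from both. Interpolation is used only for sensor-level analysis or display, and is applied after ICA.

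The article should also say whether band power is analysed at sensor or source level, since that decides whether interpolation is needed at all.

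The cost is a few sentences and a pipeline setting, with no new data. Some recordings lose a few good channels. Applying the rule to each contrasted pair keeps this loss small; a single set across all seven single-acupoint acquisitions and the other recordings could remove more of the 64 sensors. Sensor sets will still differ between participants, which this change does not remove.
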